### Intervention program

#### Study process

The overall implementation of the intervention process lasts 18 months, in which five main components are to be implemented: raising awareness about stigma and its effects on MISUI PHC users, developing a team of local champions, innovative contact-based education, analysis of internal policies, procedures, and protocols, and recovery-based arts. The entire stigma reduction intervention process will be developed between months 13 and 36 (Figure 4).

**FIGURE 4 F4:**
[figure not shown]
Intervention implementation process.

To exemplify the intervention program and timeline process, they will be described briefly accordingly to its specific objectives and their corresponding components.

#### Specific objective 1: Adapt the anti-stigma intervention with input of primary health care providers and users

An exploratory research and adaptation of the intervention will be developed during months 1–12, before the intervention. Once CESFAMs are recruited, situational assessments will be conducted in order to better understand the specific characteristics of each CESFAM to determine the logistics of implementing the intervention locally. Special emphasis will be placed on identifying the cultural and socio-demographics features of the organizations and the communities being served, to ensure that the intervention is tailored to address their specific needs. The assessment will include requests for the following information: (1) Overview of the CESFAM (history, mission, values, vision, strategic directions), (2) Organizational chart (full description of all services and programs, with an emphasis on MISUI), (3) Demographics of users, (4) Demographics of staff, (5) Challenges and opportunities, (6) Expectations about the intervention.

Based on the framework for cultural adaptation by Barrera and Castro (72), this study includes a sequential process to adapt the anti-stigma/pro-recovery intervention developed in the Canadian setting, the FONDECYT 1160099 project (34) results, and a Community-Based Participatory Research (CBPR) consultation process. CBPR in health is a collaborative approach to research (77), in which community and researchers abilities are acknowledged. CBPR involves the collaborative participation of researchers and the community that will be affected by research in the design and process of an intervention (78). It aims to combine knowledge and action for social change to improve community health and eliminate health disparities (77). This approach is implemented in order to improve the intervention relevance, adaptability and validity for the community. It also allows to access to PHC workers and users valuable information regarding internal processes and dispositions.

#### Specific objective 2: Implement a mental illness and/or substance use issues stigma reduction intervention in Centros de Salud Familiar

The comprehensive, 18-month, recovery-oriented anti-stigma intervention is composed of five components: (1) Developing a Team of Local Champions, (2) Analysis of Internal Policies, Procedures and Protocols, (3) Raising Awareness, (4) Innovative Contact-Based Education and (5) Recovery-based Arts. Teams of leaders developed as part of the first component will assist the research team with the implementation of the anti-stigma intervention at their respective CESFAM.

The first component, “Developing a team of local champions,” consists of 3–5 PHC providers and 1–2 users at each intervention CESFAM and it will be developed in months 1–3 of the intervention. The teams will comprise some individuals who have provided critical support and input, including participating in the exploratory research phase and the CBPR adaptation of the intervention framework for the Chilean context. The teams of local champions will assist with the data collection process throughout the study by encouraging colleagues to complete questionnaires and recruit users, as well as oversee and implement the intervention at their respective CESFAMs. These teams of champions will receive training to develop their skills as leaders and support the implementation process at their CESFAM. A self-administered evaluation questionnaire will be used to assess the effectiveness of the champion training and teams of local champions will track their activities at their own CESFAM.

Regarding the second component “*Analysis of Internal Policies, Procedures and Protocols*” it will be developed during months 3–18. This component involves evaluating CESFAM policies, procedures, and protocols using an anti-stigma/pro-recovery approach to identify strengths and areas for improvement in service delivery for individuals affected by MISUI. This evaluation will be completed using a policy analysis tool developed specifically for this intervention during the Canadian project; it is based on existing frameworks, such as the *Health Equity Impact Assessment Tool (HEIA)* (79) and the *QualityRights Toolkit* (80). HEIA is a tool that can be used to identify and address potential unintended health impacts (positive or negative) of a policy, program or initiative on specific population groups through five steps; scoping, potential impacts, mitigations, monitoring an dissemination (79). QualityRights Toolkit delivers information and tools for assessing and improving quality and human rights standards in mental health and social care facilities (80). At least five policies, procedures or protocols will be selected by the local champions and then analyzed by the research team. Recommendations concerning health equity, prevention of stigma and recovery-oriented practices promotion for individuals with MISUI will be developed and shared following analysis. It will be expected from each intervention CESFAM to implement at least one recommendation and make the necessary efforts to intend to educate PHC providers about the policy change in months 7–18 of the intervention. The impact of the implemented policy change will be analyzed at end-point data analysis and 6-month follow-up.

The third component *“Raising Awareness”* will be conducted during months 1–18. Various forms of media will be used to raise awareness about stigma related to MISUI among PHC providers and users. This component will be implemented throughout the intervention. Aligned with the premises of the contact-based educational element, local champions at intervention CESFAMs will determine the type of media they would like to use; this may include images, film, music, or a combination of media. This can be posters, web platforms, social media, among others. The research team will work with local champions to develop messaging to include in the media and assist with showcasing these pieces within each intervention CESFAM. This will also depend on the CESFAM’s particular resources and media choices. This component impact will be evaluated through its acceptability, adoption, appropriateness and coverage.

The fourth component “*Innovative Contact-Based Education”* will be conducted during months 1–18, trough educational workshops in intervention CESFAM. It will include anti-stigma and recovery principles, along with specific MISUI topics relevant to PHC providers. Topics will be determined by findings from the exploratory phase, current research, best practices, and the perspectives of local champions. Topics may include (1) supporting CESFAM PHC providers in preventing stigma and promoting recovery in their practice and (2) enhancing the competencies of CESFAM PHC providers for discussing MISUI with their users, identifying MISUI signs and symptoms, and referring users to psychosocial centers for treatment. Special emphasis will be placed on cultural beliefs and values that may influence stigma related to MISUI, concurrent disorders, and inter-professional collaboration within CESFAMs and between various health agencies.

The key feature of these workshops is the contact-based educational element (81), where people with lived experience participate in developing and delivering the curriculum to CESFAM PHC providers. mhGAP materials (82) will be used as main curriculum resources. As an incentive and recognition, a diploma will be given to participants. This component will be evaluated by the training team after each workshop to determine feasibility, coverage and perceived workshop usefulness.

Finally, the *“Recovery-Based Arts”* will be developed through months 7–18. Local champions at intervention CESFAMs will select one PHC provider member and recruit one artist to develop an arts curriculum and facilitate the art sessions. The facilitators will select an art form (e.g., painting, sculpting, music, sewing etc.) to use throughout the sessions. The facilitators, in collaboration with local champions, will determine themes related to MISUI to cover in each session. Ten users affected by MISUI and at least three CESFAM PHC providers will participate in the workshops each week. At the end of the 10-week program, each CESFAM will host an exhibition to showcase the artwork that has been produced.

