### Sample, recruitment, and randomization of Centros de Salud Familiars

*Servicios de Salud* will be approached and invited to participate. CESFAMs that satisfy the inclusion/exclusion criteria within participating *Servicios de Salud* will be progressively invited to participate in the study. About 50% of CESFAMs in the Metropolitan Region will be recruited, 25% in the North and 25% in the South of Chile. Once the 16 CESFAMs that satisfy the criteria are selected, they will be randomly assigned to intervention and control conditions, within each of the three mentioned geographical areas. The nature of the intervention and cluster randomized design of the study requires application to the entire CESFAM (census approach), not to individual PHC providers.

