CESFAM users will be recruited for participation in baseline and end-point data collection regarding their experiences of stigma by PHC providers. These users must be over the age of 18, have received treatment for MISUI at the CESFAM in the 3 months prior to participation (though not necessarily by a mental health professional), and have a MISUI diagnosis. User MISUI may be diagnosed by a health practitioner or self-diagnosed. Since stigma is a barrier to seeking and receiving help, it is important to include participants who have not been formally diagnosed by a healthcare provider. A research team member will approach users at the waiting room and screen them for inclusion and exclusion criteria. Users in capacity to consent will be invited to sign the consent form and those who sign will be part of the face-to-face survey assisted by a research team member on the same day in the same health facility. To assess capacity to consent, a Spanish adaptation of dimensions and criteria of the Macarthur Competency Assessment Tool for Clinical Research (MACCAT-CR) (95) are used. This process includes the following actions; (1) The interviewer exposes the user to the relevant information of the project after which he/she is questioned about what has been explained (comprehension); (2) Subsequently, they are asked about their appreciation or assessment of the information provided in their specific circumstances; and (3) A reasoned reflection on the decision to be made is promoted, assessing the circumstances and consequences, to end up expressing their choice.

The primary outcome for users will be measured using The Internalized Stigma of Mental Illness (ISMI) scale, validated for the Chilean population (96). The study will collect cross-sectional samples at baseline and end-point data collection and compare average scores between intervention and control groups for baseline and end-point measures.

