## Ethics and dissemination

a. Research Ethics Approval

This protocol and the template and site-specific informed consent forms, recruitment materials and other requested documents were reviewed, analyzed and approved by the sponsor and the applicable Pontificia Universidad Católica de Chile Ethics Committee (EC) (ID::190603010), Herminda Martin de Chillán Hospital EC, Valparaiso Health Service EC, Coquimbo Health Service EC and Reloncavi Health Service with respect to scientific content and compliance with applicable and intervention research and human subjects regulations. The proposal will follow all ethical guidelines provided for conducting research with human beings. The proposal, interim reports and final reports will be submitted to the EC’s at the beginning, middle, and end of the study.

b. Consent

All participants will be required to read and sign an informed consent form outlining the aims and objectives of the study prior to engaging in any aspects of the project, particularly before participating in the data collection process. It will be presented comprehensibly, the opportunity to ask questions will be given, understanding confirmation will be solicited, and voluntarily participation will be re assured. All user participants will also receive an oral explanation of the consent process prior to signing and/or agreeing to participate, and PHC user capacity to consent will be considered.

Informed consent will be conducted by interventors/researchers/PHC workers, guaranteeing adequate training and experience, in order to protect participants moral wellbeing and human rights. The consent process will be conducted by trained professionals.

c. Confidentiality

All participants will be assigned a numerical code, resulting in the anonymization of data. All knowledge translation materials will only include data for groups with 10 members or more to protect confidentiality. Although the quantitative surveys include a question about the participant’s CESFAM, reports for each CESFAM will be general and will not include a separate analysis by profession, limiting the potential to identify individual respondents.

d. Ancillary and Post-Trial Care

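### Local champions exist only at intervention CESFAMs, yet are given a part in recruiting surveyed users and prompting questionnaire completion; this risks selection bias by arm, mainly in the user outcome (ISMI)

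*Protocol article*

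**What the plan says.** All sections cited are in the protocol article.

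- **Allocation.** Sample, recruitment, and randomization: "Once the 16 CESFAMs that satisfy the criteria are selected, they will be randomly assigned to intervention and control conditions".
- **Who the champions are.** Specific objective 2 says the champion component "consists of 3–5 PHC providers and 1–2 users at each intervention CESFAM and it will be developed in months 1–3 of the intervention". The teams therefore exist in one arm only and form after allocation.
- **What they do.** The same section states: "The teams of local champions will assist with the data collection process throughout the study by encouraging colleagues to complete questionnaires and recruit users", and the sentence continues "as well as oversee and implement the intervention at their respective CESFAMs". Nothing equivalent is described for control CESFAMs.
- **How users are recruited.** Specific objective 3, quantitative component: "A research team member will approach users at the waiting room and screen them for inclusion and exclusion criteria". Consent and the survey follow on the same day at the same facility. No difference by arm is stated. Separate cross-sectional samples are taken at baseline and end-point.
- **Who counts as eligible.** "User MISUI may be diagnosed by a health practitioner or self-diagnosed".
- **How providers are surveyed.** The questionnaire is self-administered in both arms, in a session arranged by the CESFAM director.
- **Consent.** Ethics and dissemination: "Informed consent will be conducted by interventors/researchers/PHC workers".
- **Users inside the intervention.** On the arts component, Specific objective 2 says: "Ten users affected by MISUI and at least three CESFAM PHC providers will participate in the workshops each week".

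**The concern.** In a cluster trial, randomising the centres protects the comparison only if individuals then enter the outcome sample in the same way in both arms. Here, people who know the allocation and deliver the intervention are given a part in assembling the outcome data, and only in their own arm.

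The user outcome is the more exposed. The end-point sample is drawn afresh after the intervention, so whoever is recruited then fixes the mean that is compared. The users whom champions know best are likely to be those already engaged with the intervention, and no text excludes or flags them.

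Providers are exposed to a lesser degree. The Discussion's own limitations paragraph says that those who respond may be the more tolerant staff. Prompting by colleagues in one arm can therefore make non-response differ by arm. That paragraph lists non-response, social desirability and lack of blinding, but not recruitment support that differs between arms.

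**Working it through.** **1. The texts side by side.** Specific objective 2 gives champions a role in data collection for the whole study. Specific objective 3 gives the approach and screening of users to the research team. The consent paragraph names three kinds of people without saying who takes consent for which participants. These do not add up to one recruitment procedure common to both arms. The sentence on champions can mean that champions recruit users or that they encourage colleagues to do so. The asymmetry between arms is the same under either reading.

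**2. Which data waves are affected.** Teams form in months 1–3 of the intervention and baseline is taken before it. The asymmetry therefore bears mainly on the user end-point sample and on the provider mid-point, end-point and follow-up waves.

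**3. The plan's own figures (they reproduce).** Two-sided α 5%, power 80%.
- Users: difference = 10.34 × (0.15 − 0.01) = 1.4476; SD 4.74. n = 2(1.96 + 0.8416)² × 4.74² / 1.4476² gives 169 per arm, as stated.
- With ICC 0.01 and 8 clusters per arm: m = 169 × 0.99 / (8 − 169 × 0.01) = 26.5, so 27 per CESFAM and 216 per arm, as stated.
- Providers: difference 3.4, SD 8.3 gives 94; 94 / 0.9 gives 105, as stated.

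Nothing in this point rests on an error in the sample size.

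**4. Upper bound on users from within the intervention.** Ten arts users plus 1–2 user champions: (10 + 1)/27 = 0.41 and (10 + 2)/27 = 0.44. This ceiling is reached only if every one of them is eligible and surveyed.

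**5. Illustration for ISMI (assumed inputs).** Bias = share of the intervention sample coming through champions × score difference.
- Low: 0.20 × 1 = 0.20 points; 0.20 / 1.4476 = 14% of the planned effect.
- High: 0.44 × 2 = 0.88 points; 0.88 / 1.4476 = 61%.
- If champions bring in nobody, or those they bring in score like other users, the bias is 0.

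Standard error of the arm difference: design effect = 1 + 26 × 0.01 = 1.26; SE = 4.74 × √(2 × 1.26 / 216) = 0.512. With no true effect, the chance of a significant result is Φ(−1.96 + b/SE) + Φ(−1.96 − b/SE). This is about 7% at b = 0.20 and about 41% at b = 0.88, against a nominal 5%.

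**6. Illustration for OMS-HC (assumed inputs).** Suppose response is 90% in the intervention arm and 75% in the control arm, with non-responders 4 points more stigmatising. Responders then understate the full-staff mean by 0.10 × 4 = 0.4 and 0.25 × 4 = 1.0 points. The contrast shifts by 0.6 points against the intervention, or 0.6 / 3.36 = 18% of the planned difference (48 × 0.07 = 3.36).

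Recruiting more participants would remove neither shift.

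**The case against.** The strongest reply is that champions only assist, and that Specific objective 3 sets out the actual procedure: a research team member approaches, screens and surveys users, with no distinction by arm. Champions might do no more than mention the survey. This stands to a degree. A reader might infer that champions select the user sample, or that selection is known to differ by arm; the text does not go that far. But Specific objective 3 does not exclude champion recruitment and Specific objective 2 provides for it, so the conflict remains.

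Other points that stand:

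- The consent sentence is a general list covering all participants, including surveyed providers. It does not assign user-survey consent to PHC workers; it merely fails to rule that out.
- The provider risk is the weaker one. All providers with direct user contact are to be recruited, both arms have a session set by the director, and the illustrated shift works against the intervention.
- The 41–44% leans high. Eligibility requires MISUI treatment in the previous 3 months, the arts programme lasts 10 weeks, and each CESFAM serves at least 15,000 people. Lower scores among arts participants may also be partly true effect; the distortion would lie in over-representing them.
- It would be too strong to say that no analysis can help. Baseline data, covariates and repeated provider measures may reduce the bias, but cannot be relied on to remove it. The social desirability scale measures response style, not who was recruited.
- Whether awareness and training change who meets the eligibility definition is a separate question that does not depend on champions.

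**Conclusion.** The concern holds as a documented difference between arms in recruitment support, together with an unresolved conflict between sections. As written, people who implement the intervention have a part in recruiting users and prompting questionnaires at intervention CESFAMs only. The main risk is selection bias in the end-point ISMI comparison; differential provider response on OMS-HC is secondary.

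The documents do not establish the size or direction of any bias. The 11–12 users out of 27 are a ceiling. The 0.2–0.9 ISMI points (14–61% of the planned difference) depend on an assumed champion-sourced share of 20–44% and an assumed gap of 1–2 points, and zero is also possible. A reader might take these figures as an estimate of bias, or conclude that both primary outcomes are compromised; neither follows. What does follow is that the procedure should be settled before end-point recruitment, because selection cannot be reliably undone afterwards.

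**What to change.** 1. In Specific objective 2, remove champions from user recruitment and from outcome data collection, including prompting colleagues to complete questionnaires.
2. State in Specific objective 3 that the waiting-room procedure, carried out by research team members, applies identically in all 16 CESFAMs. Use the same director-scheduled provider session and the same reminders in both arms.
3. Record whether each surveyed user was an arts participant or a champion, and run a sensitivity analysis without them. Such users exist only in the intervention arm and may carry real effect, so this analysis should support the main one and not replace it.
4. Reconcile Specific objective 2, Specific objective 3 and the consent paragraph, so that PHC workers do not take consent for the user survey.

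The cost is protocol wording, one or two extra survey items and possibly slower recruitment at intervention sites. The sample size does not change.

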#### Specific objective 3: Evaluate the effectiveness of the intervention in primary health care

This part of the interventions is composed by a quantitative and a qualitative component.

1. a Quantitative Component:

All PHC providers at the selected CESFAMs who have direct contact with users will be recruited for the study and will be expected to participate at all data collection time-points. A total sample size of at least 36 PHC providers per CESFAM with a total of 288 per arm its estimate (or 576 per data collection). Sample size for the proposed study was calculated in two steps. First, it was calculated with individual randomization. This calculation was based on the mean ± SD score for the OMS-HC scale was 48 ± 8.3 points, estimated with a sample of 798 PHC providers surveyed in FONDECYT N° 1160099 (34). This should be the average obtained in control CESFAM for the present study. Based on prior interventions in Canada (63), an estimated effect size of 10% in the intervention arm and a placebo effect of 3% in the control arm (from survey application) is expected. Thus, the average OMS-HC score in the intervention arm is expected to decrease to 43.2 ± 8.3 in the intervention group and 46.6 ± 8.3 in the control group (representing a decrease of 4.8 and 1.4 points, respectively). The standard deviation was assumed to remain the same in the intervention and calculations. To detect a statistically significant difference between intervention and control CESFAM, with an α = 5% and statistical power of 80%, the minimum sample size per arm is 94 individuals. Considering a 10% loss to follow-up in the intervention arm, 105 individuals per arm should be recruited with an individual randomization design. The minimum sample size was also calculated considering cluster randomized controlled design. Two elements were considered: (1) a minimum sample size of 105 and (2) an estimation of the intracluster correlation coefficient (ICC) for the study outcome (OMS-HC scale) (83). In this case, it was assumed the ICC to be ρ = 0.05, which is consistent with highest value reported in the literature for outcomes in primary care settings (74) and slightly higher than that reported in a study of a depression program in CESFAMs in Chile (84). Given the required sample size calculated based on individual randomization and the value of ICC = 0.05, the minimum number of clusters required is equal to: [105*0.05] = 5 clusters (75). However, a larger number of clusters would allow recruitment of a smaller number of individuals per cluster, maintaining an α = 5% and statistical power of 80% to detect differences between the control and intervention groups (85). For example, if 8 clusters per arm is considered (16 CESFAM total), it is necessary to recruit a minimum of 36 professionals per CESFAM. Thus, a minimum of the total sample of PHC providers to recruit would be 288 per arm (576 total). The validated, Chilean version of the Opening Minds Scale for Health Care Providers Scale (OMS-HC) (86), will be used as the primary outcome measure for PHC Professionals in the study. It will be applied at baseline, mid-point, end-point, with an expected 9-month interval between applications, and at 6-month follow-up.

A self-administered questionnaire will be used to examine stigma directed at persons with MISUI among health professionals. Five existing scales to measure stigma toward MISUI were selected to include in the questionnaire because they had been validated in Chile and were recommended by the research team. These scales reflect the current state of knowledge about stigma measurement (with a focus on health providers and persons with MISUI), as well as the feasibility of implementation at CESFAMs. They include: the Opening Minds Scale for Health Care Providers OMS-HC (83, 87, 88), Mental Illness: Clinicians’ Attitudes (MICA) (89), Modified Bogardus Social Distance Scale (90, 91) or Grandon Social Distance Scale (92), Recovery Scale for Providers (RS) (93), and the Recovery Self-Assessment-Revised (RSA-R) scale (94).

This questionnaire will be completed at four time-points (baseline, mid-point, end-point, and 6-month follow-up). It will collect data related to two main components: (1) socio-demographic and other relevant general variables; and (2) attitudes toward MISUI stigma and recovery. The end-point questionnaire will also include a third component focusing on the intervention and its implementation. A self-administered questionnaire will be provided to PHC providers at each CESFAM (intervention and control) at a time set aside by CESFAM directors.

CESFAM users will be recruited for participation in baseline and end-point data collection regarding their experiences of stigma by PHC providers. These users must be over the age of 18, have received treatment for MISUI at the CESFAM in the 3 months prior to participation (though not necessarily by a mental health professional), and have a MISUI diagnosis. User MISUI may be diagnosed by a health practitioner or self-diagnosed. Since stigma is a barrier to seeking and receiving help, it is important to include participants who have not been formally diagnosed by a healthcare provider. A research team member will approach users at the waiting room and screen them for inclusion and exclusion criteria. Users in capacity to consent will be invited to sign the consent form and those who sign will be part of the face-to-face survey assisted by a research team member on the same day in the same health facility. To assess capacity to consent, a Spanish adaptation of dimensions and criteria of the Macarthur Competency Assessment Tool for Clinical Research (MACCAT-CR) (95) are used. This process includes the following actions; (1) The interviewer exposes the user to the relevant information of the project after which he/she is questioned about what has been explained (comprehension); (2) Subsequently, they are asked about their appreciation or assessment of the information provided in their specific circumstances; and (3) A reasoned reflection on the decision to be made is promoted, assessing the circumstances and consequences, to end up expressing their choice.

The primary outcome for users will be measured using The Internalized Stigma of Mental Illness (ISMI) scale, validated for the Chilean population (96). The study will collect cross-sectional samples at baseline and end-point data collection and compare average scores between intervention and control groups for baseline and end-point measures.

A minimum sample size of 27 PHC users per CESFAM was calculated (or 216 users per study arm, or 432 users total per data collection). For this sample size calculation, the mean ± SD for the ISMI score was 10.34 ± 4.74 points, estimated based on the results of FONDECYT N° 1160099 (34). A placebo effect of 1% was considered in the control group, and a 15% expected effect size was considered in the intervention group, based on the protocol for a similar intervention study completed in Canada (which estimated a higher effect of 19.5%; a more conservative estimate was selected for this calculation) (64). Thus, the mean of the scale would decrease to 10.23 ± 4.74 in the control group and to 8.79 ± 4.74 in the intervention group (an average decrease of 0.1 and 1.55 points, respectively). No change in the standard deviation was assumed, to be conservative with the calculation. To detect a statistically significant difference of this size between intervention and control groups, with a significance level of α = 5% and statistical power of 80%, 169 individuals are required in each group (intervention and control). Loss to follow-up it is not considered, as individuals recruited at the baseline and end-point data collection will not necessarily be the same, and this will be a cross-sectional sample. In the cluster RCT design, it is expected that the ICC of the ISMI score would be relatively low, as the CESFAM user population is more likely to be heterogeneous than the PHC providers. Assuming an ICC = 0.01, and considering the k = 8 clusters in each arm of the study (from PHC provider calculations), or 16 CESFAM total, it is necessary to recruit a minimum of 27 PHC users per CESFAM, or 216 users in each arm, for a total sample size of 432.

A face-to-face survey assisted by a research team member will be used to examine how users perceive stigmatizing attitudes and behaviors among CESFAM PHC (97) providers. The questionnaire will include four main components: (1) socio-demographic and other relevant general variables; (2) perceived stigmatizing attitudes and behaviors among CESFAM PHC providers; (3) perceived recovery-oriented practices by CESFAM PHC providers; and (4) accessing healthcare at their CESFAM. Subjective experience of stigma as conveyed by CESFAM PHC providers will be measured among patients using validated tools. The Perceived Devaluation-Discrimination Scale will be used to assess the extent to which users believe that other people devalue or discriminate against someone with MISUI. This scale has shown acceptable internal consistency (*a* = 0.78) (97). The tool is validated in Chile (98). An adapted version of the Discrimination Experience Subscale of the 29-item ISMI scale was designed to measure the subjective experience of stigma, e.g., respondents’ perceptions of how they are treated by others. It measures alienation, stereotype endorsement, perceived discrimination, social withdrawal, and stigma resistance. The Cronbach’s alpha value of the total score was 0.83 and the Spearman-Brown Coefficient of 0.76 (99). For FONDECYT N° 1160099 (34), a shortened version of the ISMI scale was used, which was validated for use in Chile with an (*a* = 0.916) (96). The Person in Recovery Version of the RSA will also be considered to assess users’ perceptions of recovery-oriented practices in their CESFAMs. Due to the sensitive nature of the study scales, there is some risk of social desirability bias in participants’ responses. Both PHC providers and users will complete the Marlowe-Crowne Social Desirability Scale (MCSDS). The MCSDS will allow to measure and control such bias. The scale has 33 items which were defined to be culturally acceptable but unlikely to occur, and to have minimal abnormal implications for either the socially desirable or socially undesirable responses (100).

1. b Qualitative component:

To evaluate implementation of the intervention, qualitative interviews will be held with two PHC providers (local champions) and one CESFAM authority per intervention site at baseline, mid-point, and end-point. In addition, at least one local champion from the community will be interviewed to explore his/her/they experience as a champion, pros and cons of the intervention and how it could be improved. Questions will relate to implementation outcomes for the intervention: acceptability, adoption, appropriateness, feasibility, fidelity, implementation cost, coverage and sustainability (101). In addition, mid-point, end-point, and follow-up questionnaires administered for PHC professionals in experimental CESFAMs will include questions regarding: acceptability, adoption, appropriateness, feasibility, fidelity, implementation cost, coverage, and sustainability. End-point interviews will also include questions regarding key elements needed for scaling up the intervention. In addition, near to the culmination of the project, a Symposium with 20–30 key stakeholders including members from the Ministry of Health, *Servicios de Salud* and CESFAMs, among others, will be held in order to define final recommendations to scale up the anti-stigma intervention on a national level. The discussion process will be guided through ExpandNet & WHO Framework (102) and the recent theoretical recommendations from Greenhalgh and Papoutsi (103) regarding scaling up processes in health, as well as the critical aspects about dissemination of stigma reduction interventions identified by Kemp et al. (69).

*Specific Objective 4* corresponding to “*identify critical barriers and opportunities for its implementation in PHC”* and *Specific Objective 5, “Develop recommendations to scale up the anti-stigma intervention”* will be developed by the qualitative component of data previously mentioned.

A brief summary of the study’s activities is described, correlated with the project timeline in Figure 5.

